## Abstract

**Background:**

Challenging behaviors exhibited by individuals with dementia might result from an unmet need that they cannot communicate directly due to cognitive restrictions. A dementia-specific case conference represents a promising means of analyzing and exploring these unmet needs. The ongoing FallDem study is a stepped-wedged, cluster-randomized trial evaluating the effects of two different types of dementia-specific case conferences on the challenging behaviors of nursing home residents. This study protocol describes the process evaluation that is conducted, along with the FallDem study.

The goal of the process evaluation is to explain potential discrepancies between expected and observed outcomes, and to provide insights into implementation processes and recruitment strategies, as well as the contexts and contextual factors that promote or inhibit the implementation of dementia-specific case conferences.

**Methods/Design:**

The process evaluation will use a mixed-method design comprising longitudinal elements, in which quantitative and qualitative data will be gathered. Qualitative data will be analyzed using content analysis, documentary analysis and a documentary method. Quantitative data (standardized questionnaires) will be analyzed using descriptive statistics. Both types of data will complement one another and provide a more comprehensive picture of the different objects under investigation.

**Discussion:**

The process evaluation will allow for a comprehensive understanding of the changing processes and mechanisms underlying the ‘black box’ of the complex intervention of the FallDem study. These findings will provide practical knowledge regarding issues related to the implementation of dementia-specific case conferences in nursing homes.

**Trial registration:**

Current Controlled Trials identifier: ISRCTN20203855, registered on 10th July 2013.

## Background

Living with dementia is complicated by the presence of behavioral and psychological symptoms, which are sometimes also referred to as challenging behaviors [1]. People with dementia residing in nursing homes frequently exhibit these challenging behaviors [2], which include wandering, physical aggression, screaming, depression and resistance to receiving help with activities of daily living [3]. Rather than cognitive dysfunction, functional impairment or physical dependence, these behaviors constitute one of the greatest burdens for professional caregivers in nursing homes [4]. Challenging behaviors of people with dementia can have multiple etiologies that differ among individuals and settings. According to the need-driven dementia-compromised behavior (NDB) model, these behaviors result from an unmet need, and if they are responded to appropriately, patients’ quality of life will be enhanced [5]. A dementia-specific case conference represents a promising means of analyzing and exploring the unmet needs of people with dementia [6, 7]. Two different approaches to the dementia-specific case conference have been most commonly described in the literature [8]. The first approach entails the use of an assessment instrument to systematically guide nursing staff through the diagnostic process of a case conference (WELCOME-IdA; Innovative dementia-oriented Assessment) [9, 10]. The second approach involves the use of an open-thinking method to determine the potential triggers and causes of challenging behaviors rather than an assessment instrument (WELCOME-NEO) [11]. However, thus far, it is unclear whether the use of assessment instruments in dementia-specific case conferences are effective in supporting nursing teams in the diagnostic processes of need-driven behaviors [8]. Additionally, the advantages of dementia-specific case conferences using an open approach (without a standardized assessment) have not been explored in detail [12] or assessed in terms of their effectiveness.

The ongoing FallDem study (dementia-specific case conferences) is a stepped-wedged, cluster-randomized trial that aims to evaluate the uses of these two different types of dementia-specific case conferences (WELCOME-IdA and WELCOME-NEO) in 12 nursing homes [13]. This study is investigating whether these case conferences have an impact on residents´ challenging behaviors (primary outcome), quality of life and psychotropic drug use, as well as on the burnout and work-related stress experienced by nursing staff and their vocational action competences (secondary outcomes).

Because an effectiveness study is limited in its ability to provide information regarding whether an intervention is successful [14, 15], the FallDem study is being accompanied by a process evaluation, which is the main focus of the current study. A process evaluation provides insight into the so-called ‘black box’ of an effectiveness study and explains deviations between expected and observed outcomes. It further contributes to the understanding of how and to what extent an intervention is implemented in daily practice [16–19]. Furthermore, it provides information about the manner by which findings might be transferred across settings and populations [17, 20].

The process evaluation is of particular importance in the FallDem study because it is a dementia-specific case conference representing a complex intervention with interacting components [13] that will probably need time to be implemented in daily practice. It can be assumed that a dementia-specific case conference will have a delayed treatment effect [21] because teams in nursing homes have to learn how to employ it. This assumption needs to be further explored and defined in the process evaluation. Information about delayed treatment effects can subsequently aid in the design of a generalized linear mixed-effects model for the FallDem effectiveness study [13].

For the current study, the framework suggested by Grant *et al*. for designing process evaluations of cluster-randomized trials seems to be suitable because it considers ‘delivery to clusters’, the ‘responses of individuals’ and the ‘responses of clusters’ as essential domains to be studied [16]. These data can provide important evidence regarding the implementation success of an intervention [22]. Delivery to clusters includes information about how an intervention was delivered to each participating cluster and whether it was delivered as intended. Cluster variations in the delivery of an intervention might explain differences in its implementation and therefore variations in outcomes between clusters [16]. Response of individuals refers to the manners in which individuals in a target population react to a delivered intervention, for example, their attitudes, learning processes and behavioral changes [23]. If an intervention is not accepted by participants, the success of its implementation can be questioned [19]. Response of clusters describes how the intervention was adopted by each participating cluster. Differences in the adoption of clusters might also explain variations in outcomes [16].

The framework suggested by Grant *et al*. also includes the ‘recruitment of clusters’, ‘recruitment and reach of individuals’ and ‘context’ as areas to be studied in a process evaluation. These domains can help to assess the external validity of an effectiveness study [16]. Recruitment of clusters focuses on the strategies used by the research team to recruit clusters and the reasons why clusters decide (or not) to participate. Recruitment and reach of individuals describes the processes by which clusters identify and enroll individuals for an intervention and the proportion of recruited individuals who actually receive the intervention [16]. Information about recruitment and reach of clusters and individuals is important for deciding whether participants are representative of a target population [19]. A thorough description of the context in which a trial and intervention is embedded is of great importance for the generalization of findings, providing further relevant information about contextual factors that might act as barriers or facilitators to the implementation of the intervention [16, 18], thereby impeding or strengthening its effects [17]. In summary, the framework suggested by Grant *et**al*. [16] combines domains that are important for evaluating the implementation success of an intervention or that are crucial for judging the external validity of an effectiveness study, explaining why this specific framework was used to design the process evaluation of the FallDem study.

Due to the complexity of dementia-specific case conferences, a comprehensive implementation strategy has been developed based on expert consultation to support the cluster-randomized controlled trial, in which case conferences are employed in daily practice. This strategy follows a step-wise plan and consists of the following six components: (1) information about the research project and dementia-specific case conferences, (2) kick-off meetings, (3) in-service training on dementia and moderator skills, (4) the establishment of a steering group, (5) reminders and (6) a telephone hotline (see Table 1). Although the effectiveness of the implementation strategy for the FallDem study will not be evaluated, knowledge about the usefulness of this strategy will be important for future implementations of dementia-specific case conferences in nursing homes. Therefore, four of the six domains of the process evaluation will be expanded to create a comprehensive implementation strategy, as shown in Figure 1.

**Table 1 Tab1:** **Components of intervention and implementation strategies**

Components of intervention and implementation strategies		Content	Participants (target population)	Duration
Components of the intervention	I. In-service training in performing case conferences	▪ Aims and structures of CCs, NDB model, communication rules and use of IdA (only in the WELCOME-IdA intervention group)	▪ Manager of nursing home, head nurses of nursing teams and members of nursing teams (core team)	▪ Half a day
	II. Case conferences with support (training on the job)	▪ CCs are conducted with the support of trainers; the trainers assist the moderator, are involved in discussions and provide advice	▪ Members of nursing teams (core teams) and trainers	▪ 4 CCs within 3 months
	III. Case conferences without support	▪ CCs are conducted without aid	▪ Members of nursing teams (core teams)	▪ Minimum of 4 CCs within 4 months
Components of implementation strategy	(1) Information about project/case conferences	▪ Information concerning the project/intervention and data collection, time frame and organizational aspects	▪ Manager of nursing home, quality management and head nurses of nursing teams	▪ 3 hours
	(2) Kick-off meetings	▪ Information concerning project/intervention and data collection, time frame, and organizational aspects	▪ Nursing teams	▪ 1.5 hours
	(3) In-service training in a) dementia and challenging behaviors; and	▪ a) Diagnosis of dementia, forms and symptoms of dementia, causes of challenging behaviors and their management; and	▪ a) Nursing teams (core teams)	▪ a) Half a day
	b) Moderation of case conferences	▪ b) Training in moderation techniques	▪ b) 2 persons from each nursing team	▪ b) 2 days
	(4) Establishment of steering group	▪ Development of an implementation plan	▪ Manager of nursing home, quality management and members of both nursing teams (core teams)	▪ 2 days
	(5) Reminders	▪ Reminders via telephone to conduct CCs regularly	▪ All participants	▪ During intervention
	(6) Telephone hotline	▪ Questions concerning CCs	▪ All participants	▪ During intervention

**Figure 1 Fig1:**
[figure not shown]
**Domains of process evaluation.**

Thus, thirteen research questions will guide the process evaluation, as shown in Table 2.

**Table 2 Tab2:** **Research questions of process evaluation**

	Domain	Research question
Intervention	Delivery to clusters	1. Was the intervention delivered as intended to each nursing home (cluster)?
	Response of individuals	2. Which learning processes of the target population took place in response to the intervention?
		3. What is the attitude of the target population toward the intervention?
	Response of clusters	4. How was the intervention adopted by each nursing home (cluster)?
	Recruitment of cluster	5. How were nursing homes (clusters) sampled and recruited for the FallDem study?
		6. Why have the nursing homes participated (or not) in the FallDem study?
	Recruitment and reach of individuals	7. How were participants in the intervention recruited by the cluster, and which individuals in the target population actually received the intervention?
	Context	8. What is the context in which the intervention is being implemented?
		9. What contextual factors promoted or inhibited the implementation of the intervention?
Implementation strategy	Delivery to clusters	10. Was the implementation strategy delivered as intended for each nursing home (cluster)?
	Response of individuals	11. What is the attitude of the target population toward the implementation strategy?
	Response of cluster	12. How was the implementation strategy adopted by each nursing home (cluster)?
	Recruitment and reach of individuals	13. How were the participants in the implementation strategy recruited by the nursing homes (clusters), and which individuals in the target population actually received the implementation strategy?

## Methods/Design

### Study design

The process evaluation is a mixed-method study comprising longitudinal elements, for which quantitative and qualitative data are gathered (Tables 3 and 4). This method will be carried out alongside the FallDem study [13]) between September 2013 and March 2015. A total of 12 nursing homes (clusters) located in the area of North-Rhine-Westphalia (Germany) will take part in the process evaluation. The inclusion criteria for the clusters have been previously published elsewhere [13].

In the FallDem study, the intervention is rolled out every three months to two nursing homes (cluster group) over a period of 18 months (stepped-wedge design). Within every cluster, two nursing wards, which each include one nursing team (core team), participate in the intervention. The order in which the 12 nursing homes will receive the intervention and the type of intervention are determined at random (six WELCOME-IdA clusters and six WELCOME-NEO clusters). Two nursing teams that belong to one cluster will receive the same type of intervention to avoid contamination between WELCOME-IdA and WELCOME-NEO. The last group of clusters includes four instead of two clusters because two nursing homes functioning as cluster reserves will be dropped before the end of the study (Figure 2).

The intervention phase (in-service training during case conferences, on-the-job training and case conferences with support) for each cluster lasts seven months, after which a follow-up phase, which lasts until the end of the data collection period for all 12 clusters (T6), occurs. Hence, the intervention phase is the same duration for each nursing home, but the durations of the pre-intervention and follow-up phases differ (Figure 2).

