#### Context of intervention

The context in which the intervention is implemented will first be assessed through a semi-structured telephone interview [37] with the head nurse of each participating nursing ward at the beginning of the FallDem study (data source K). The telephone interview will aim to explore whether nursing teams already have experience in performing dementia-specific case conferences and, if they do, which factors promote or inhibit their performance. Second, the public area of each participating nursing ward will be evaluated with the Dementia Milieu Assessment (DMA) [39]. The DMA assesses the ‘dementia-friendliness of environments’ and will be conducted during a two-hour observation period from 3 to 5 pm. The DMA will be used at the beginning and end of the FallDem study (data source L). Third, a standardized questionnaire will be used quarterly (T0 to T6) to assess the organizational characteristics of the 12 participating clusters and 24 participating nursing wards (such as the size, number of employees, types of living arrangements, staff specialization and characteristics of residents) (data source M).

To gain insight into the contextual factors that promote or inhibit the implementation of dementia-specific case conferences, all data sources of the process evaluation (A to N) will be used and secondarily analyzed. No additional data will be gathered to answer this research question. For the process evaluation of the implementation strategy, seven different data sources (A, C, F, G, H, I and J), which are summarized in Table 4, will be used.

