#### Defining delayed treatment effect

It can be assumed that a dementia-specific case conference shows its full treatment effect (100%) when it is delivered over time as intended, is accepted by the nursing team and is adopted by the nursing home. The earliest time point at which a full effect could be expected according to the data is at the transition from training on the job (II) to case conferences without support (III). However, case conferences represent complex interventions that require training and education (as expected, the staff may need more time to learn how to use the case conferences in their daily work routines). Therefore, a delayed treatment effect cannot be excluded (for example, the intervention being only 75% effective after transition from training on the job (II) to case conferences without support (III)). This information provided by the process evaluation will be important for improving model building using a generalized linear mixed-effects model of the effectiveness study. The delay must be modeled as a fractional treatment effect in the mixed-effects model as described by Hussey and Hughes [21]. To define a possible delayed treatment effect for each nursing home, the data pertaining to the delivery of intervention to clusters, the response of individuals to the intervention and the response of clusters to the intervention will be used.

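### As the schedule is written, the last group of homes reaches T6 before or just as its seven-month intervention phase ends, so the follow-up phase described for it cannot occur.

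*Protocol article*

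**What the plan says.** All the timing statements but one are in the protocol article's Study design section.

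- Rollout: "the intervention is rolled out every three months to two nursing homes (cluster group) over a period of 18 months".
- Size: 12 homes take part, and "The last group of clusters includes four instead of two clusters". The reason given is that two homes serve as reserves and are to be dropped before the study ends.
- Phase: each home's intervention "lasts seven months, after which a follow-up phase, which lasts until the end of the data collection period for all 12 clusters (T6), occurs". The text adds that this phase is equally long for every home and that only the pre-intervention and follow-up periods vary. Table 1 supports the seven months: three months of supported case conferences plus four months of unsupported ones.
- Calendar: the process evaluation runs "between September 2013 and March 2015".
- Waves (Context of intervention): "a standardized questionnaire will be used quarterly (T0 to T6").

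Tables 3 and 4 time the group interviews with moderators (source H), core teams (I) and steering groups (J) to when a home's intervention phase ends. Planned numbers are 12, 24 and 12. The Trial status section has the trial complete by the end of 2015.

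**The concern.** The step length, number of groups, phase length and close of data collection are each stated, and together they leave too little time for the last group. If so, a follow-up period is described that does not exist for these homes, and the interviews due when their phase ends cannot be held before the stated close.

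This matters beyond tidiness. Sources H, I and J inform adoption and the response domains. Those domains, together with delivery, are to define a home-specific delayed treatment effect that enters the effectiveness model as a fractional effect (Data analysis; Defining delayed treatment effect). That section fixes the reference point: "The earliest time point at which a full effect could be expected according to the data is at the transition from training on the job" to unsupported case conferences. A late home with little or no observation after that point says little about how quickly its effect builds up.

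**Working it through.** Inputs, all from the protocol article: step 3 months; 12 homes; last group of 4; phase 7 months; waves T0 to T6 quarterly; window September 2013 to March 2015. The text does not give the month in which the first group starts, so it is varied. T0 includes interviews on care as usual in all 24 teams, so the first start is taken to be no earlier than T0.

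**The plan's own figures reproduce.**
- Phase: 3 + 4 = 7 months.
- T0 to T6: 6 intervals × 3 = 18 months.
- September 2013 to March 2015: 18 months, or 19 if both end months count in full.
- Homes: 4 × 2 + 4 = 12, that is, five groups.

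**Schedule.** Start of group i = first start + 3 × (i − 1). End = start + 7. Follow-up = 18 − end.

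| Group (homes) | End, first start at T0 | Follow-up to month 18 | End, first start at T1 | Follow-up to month 18 |
|---|---|---|---|---|
| 1 (2) | 7 | 11 | 10 | 8 |
| 2 (2) | 10 | 8 | 13 | 5 |
| 3 (2) | 13 | 5 | 16 | 2 |
| 4 (2) | 16 | 2 | 19 | −1 |
| 5 (4) | 19 | −1 | 22 | −4 |

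To finish by month 18 a home must start by month 18 − 7 = 11. Starts at months 0, 3, 6 and 9 qualify, so at most four groups fit.

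**Other readings.**
- First start on 1 September 2013 and close on 31 March 2015 (month 19): the last four homes end at 12 + 7 = 19, exactly at the close, with zero follow-up.
- First start at month 3 with the same close at month 19: group 4 has zero follow-up and group 5 overruns by 22 − 19 = 3 months.
- Six groups of two, first start at T0: the last two groups end at months 19 and 22, so four homes again have no follow-up to month 18.

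**Interviews.** Planned total: 12 + 24 + 12 = 48. For a last group of four homes with two teams each: 4 + 8 + 4 = 16. If both reserves come from that group and are dropped: 2 + 4 + 2 = 8 of 40 interviews, and 2 of 10 homes.

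**Waves after the earliest full-effect point.** With a T0 start, the last group moves from supported to unsupported conferences at 12 + 3 = month 15 (T5), which leaves one later wave, T6. With a T1 start the move falls at 15 + 3 = month 18, which is T6 itself, and no later wave remains.

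**The case against.** The best defence is that the schedule is in Figure 2, which is not available here, and that the text does not give the first start month. This limits what can be said about the size of the overrun. It does not restore follow-up for the last group, because the step, the phase length and T6 are all in the text. The word for quarterly is attached to one questionnaire, but the 18-month spacing it implies agrees with the calendar window. The 19-month reading does remove the overrun with a T0 start, though it leaves zero follow-up.

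The reserve homes also count. If both are dropped from the last group, fewer homes are affected, although Tables 3 and 4 still plan for 12 homes and 24 teams.

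Four stronger readings are tempting, and the documents do not support them.

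- A reader might infer that adoption will be understated in the late homes. Nothing says that the interviews will be held early. They are tied to the end of the phase, not to T6, and the trial runs to the end of 2015. The delayed-effect definition also draws on other delivery and response sources.
- A reader might infer a fixed share of one third of homes. The count moves with the start month and with the reserves.
- A reader might take 18 months of rollout to mean six groups, hence 14 homes. Five groups give 12 without strain.
- A reader might see a further timing conflict in the Study design list of phase components, which ends with supported conferences. Table 1 gives the unsupported component clearly, so this is a wording slip.

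The Discussion concedes that maintenance is only partly addressed and that the period after the intervention is out of scope. This lowers the stakes, but it does not disclose that one group has no such period.

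**Conclusion.** The stated rollout, equal seven-month phase, follow-up to T6 and quarterly T0 to T6 cannot all hold. The direction is firm: no reading of the text gives the last group any follow-up.

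The size depends on the unstated first start month. With T6 at month 18, the overrun is 1 month for a T0 start and 4 months for a T1 start; in the T1 case six homes are affected. With a 19-month window and a T0 start it is zero. At the planned numbers, at least 4 of 12 homes and 16 of 48 group interviews fall at or after the close, subject to the reserves. Interviews held by T6 would describe an unfinished intervention in these homes (one only just ending, on the 19-month reading); interviews held later fall outside the stated window. At most one wave follows the earliest full-effect point for the last group.

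This is a should-fix. The evaluation is mixed-method with descriptive statistics, and the remedy is inexpensive. It would go too far to conclude that the follow-up statement itself is the error and should be struck out: the text does not show which of the conflicting figures is wrong.

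**What to change.** Set out one month-by-month schedule that reconciles the number of groups, each group's start, the move from supported to unsupported conferences, the end of the phase, T0 to T6 and the calendar window. It should also show when and from which group the reserve homes leave. The sponsor must decide which of the conflicting figures changes.

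If the conflict remains after that, take one of two routes:

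1. Extend process-evaluation data collection for the late group or groups, within the trial period to the end of 2015, so that H, I and J follow the actual end of the phase.
2. State that these homes give partial-intervention data without follow-up, and treat them so when defining the delayed treatment effect.

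In either case, word the follow-up statement to match the reconciled schedule.

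The cost is schedule text and, under the first route, later dates for interviews already planned (16 at the planned numbers with a T0 start; 24 if the first group starts at T1, since 6 + 12 + 6 = 24). No new instruments or participants are needed.
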